### Population

For the purposes of the analysis, two types of population are to be considered:

• Per intention to treat (ITT): this population will consist of all the randomised patients. Those taking part in the selection phase but not subsequently randomised for treatment will be excluded from this population. This will comprise the main population for analysis of the parameters of effectiveness.

• Per protocol: this population will consist of all the patients in the ITT population with no serious deviations from the protocol. This will comprise the secondary population for analysis.

### Treatment comparisons

All the tests will be bilateral and carried out at a level of significance of α = 0.05. So as not to interrupt the study, no intermediate analyses are foreseen.

### Data analysis

To describe the different baseline characteristics of the patients, we shall use measures both of position (the mean or the median, according to the asymmetry) and of variability (standard deviation or interquartile range) for the continuous variables, while the others will be described via their frequency distributions, comparing the experimental and control groups. Moreover, a graphic analysis will be made, using smoothed versions of the histograms, boxes and other representations.

For the principal result variable, the difference between the final value and the baseline Constant SFA score, measured in absolute terms, the experimental and control groups will be compared after adjusting by the baseline value and subsequently by other possible confounders. This analysis will be repeated in the follow ups at 3, 6 and 12 months. We will evaluate the effect of possible points of influence by repeating the model after exclusion of the observations with a large Cook-distance value. The assumptions of the model will be tested and reanalysed using a Q-Q plot diagram for the assumption of normality, and by comparing the studentised residuals versus the values of the independent variable for the assumption of constant variances.

For the secondary result variables, the bivariate analysis will be performed using contingency tables analysed by ji-squared tests (for tables larger than 2 × 2), by ji-squared tests corrected for continuity, or Fisher's exact test (for 2 × 2 tables), for the categoric variables, and by simple linear regression for all other cases. Two-dimensional graphs will also be used.

The multivariate analysis will depend on the nature of the response variable. When this is dichotomic, a binary logistic regression analysis will be made, and for this purpose we will establish the dummy variables needed for the categoric predictors. The inclusion of the "experimental group" or "control group" variable will be forced. The "forward procedure" method will be used to select the possible confounding variables in the model, and the entry criterion used will be the change in the likelihood ratio. The functional form of the continuous predictors will be studied via the corresponding statistical criteria, these being mainly graphic procedures.

For continuous variables, a multiple linear regression model will be used, and the same model-selection criteria and diagnostic procedures as described above will be applied.

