### Sample size and associated power

The sample size was predetermined for a level of significance of 0.05, a power of 0.80 and a final average score on Constant's SFA scale of 70 among the experimental group (standard deviation 17) and 65 among the control group (standard deviation 18), with a two-tailed test, according to data taken from Kleinhenz [17]and Sun [18]. Thus, 188 patients are required for the experimental group and 199 for the control group. Assuming a 20% dropout rate, the final sample size was set at 226 patients for the experimental group and 239 for the control group [26].

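### Repeating the single-visit regression at 3, 6 and 12 months leaves the T-1 value unused, so the follow-up effect can be biased if loss depends on early response

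*Protocol article*

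**What the plan says.** The Data analysis section of the protocol article defines the principal comparison as the change in Constant SFA score between groups, adjusted for baseline and then for other possible confounders. Multiple linear regression is the model class for continuous variables. For later visits it says: "This analysis will be repeated in the follow ups at 3, 6 and 12 months". It names no longitudinal model, and it does not say that the T-1 value enters any follow-up model.

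The Population section says of the intention-to-treat set that "this population will consist of all the randomised patients", and makes it the main population for effectiveness. The sample-size section inflates the required numbers "Assuming a 20% dropout rate".

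The primary time point is T-1, after the 15th physiotherapy session. The full SFA is scored again at T-2. At T-3 and T-4, which are telephone interviews, only its subjective part is collected (35 of 100 points). The withdrawal procedure has the study variables assessed when a patient leaves, but does not say how those values are used.

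**The concern.** A regression of one visit's value on group and baseline can only be fitted to patients who have a value at that visit, unless something is filled in. A patient seen at T-1 and lost before T-2 has a known early response that is closely relevant to the missing value, and the stated model makes no use of it.

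This matters if loss is related to early response. Patients who have not improved may seek care elsewhere, and patients who have recovered may stop attending or answering. The reasons could also differ by arm: the Discussion says that the placebo is markedly unlike the acupuncture and that a double-blind design is not possible. The follow-up comparisons are what will show whether any effect lasts, and the planned difference is only 5 points. A bias of a few points could therefore change that conclusion.

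**Working it through.** **Anchor: the plan's own figures.** The sample-size section gives means and SDs as "70 among the experimental group (standard deviation 17) and 65 among the control group (standard deviation 18", with two-sided alpha 0.05 and power 0.80. With allocation proportional to SD, n_i = s_i(s_1 + s_2)(1.960 + 0.842)² / d²:
- experimental: 17 × 35 × 7.849 / 25 = 186.8
- control: 18 × 35 × 7.849 / 25 = 197.8

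The article states that "188 patients are required for the experimental group and 199 for the control group". Power at 188/199 is 0.802, so the figures reproduce. They supply the effect of 5 points and an SD of about 17.5 (midway between 17 and 18) for what follows.

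**The two estimators at T-2.** G is group, B is baseline, Y1 and Y2 are the SFA scores at T-1 and T-2.
- *Single-visit regression:* fit Y2 = b0 + b1·G + b2·B to patients with Y2. The effect is b1. Using change instead of final score gives the same b1, because B is a covariate.
- *Joint likelihood using T-1:* fit Y1 = a0 + a1·G + a2·B to everyone seen at T-1, and Y2 = c0 + c1·G + c2·B + c3·Y1 to those seen at T-2. The effect is c1 + c3·a1.

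**Assumptions, none of them from the article:** baseline correlation 0.5; T-1/T-2 residual correlation ρ of 0.4 or 0.7; 20% loss after T-1; log-odds of loss changing by 1.0 per SD of the T-1 score; the same true effect at T-1 and T-2. Arms are 226/239, with 1,500 simulated trials per setting (Monte Carlo error about 1.6/√1500 = 0.04).

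Mean estimate from the single-visit regression on patients present:

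| Loss after T-1 | True 5, ρ 0.4 | True 5, ρ 0.7 | True 0, ρ 0.4 | True 0, ρ 0.7 |
|---|---|---|---|---|
| Unrelated to response | 4.98 | 4.98 | -0.03 | -0.04 |
| Poor responders, both arms alike | 4.87 | 4.68 | 0.01 | 0.07 |
| Poor responders, control only | 3.95 | 3.17 | -0.97 | -1.73 |
| Control poor, acupuncture good responders | 3.11 | 1.73 | -1.88 | -3.28 |

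The joint estimate is 4.96 to 5.05 for a true 5, and -0.04 to 0.06 for a true 0, in every row. For a true 5, its standard error is 1.45 to 1.62, against 1.52 to 1.62 for the single-visit regression.

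**Why the table looks like this.** The bias is approximately ρ × residual SD × (difference between arms in the mean standardised T-1 residual of those retained). The residual SD is 17.5 × √0.75 = 15.2. In the last row, 1.88/(0.4 × 15.2) and 3.28/(0.7 × 15.2) both give 0.31. In the control-only row, 0.97/(0.4 × 15.2) and 1.73/(0.7 × 15.2) both give 0.16. If there is no effect and the mechanism is the same in both arms, the retained groups do not differ and the bias is zero. By symmetry, exchanging the arms' mechanisms when there is no effect reverses the sign.

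**Sensitivity.** A separate simulation with the same SD, loss rate and true effect of 5 gave:
- poor responders leave both arms alike: 4.8 to 4.9
- both extremes leave, in both arms: 4.1 to 4.4
- control poor responders only: 3.5 to 4.2
- opposite directions by arm: 2.1 to 3.4

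Another run of the both-extremes case, at about 21% loss and correlations of 0.5 to 0.7, gave 4.5 to 4.6, and -0.1 to 0.0 when there was no effect.

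**The case against.** The strongest reply is that the article never states a complete-case rule. It names all randomised patients as the main population, has variables assessed at withdrawal, and says nothing on missing values, which a condensed article may leave to a fuller document. A visit-by-visit regression is compatible with imputation that uses T-1, and lost patients would then contribute. This stands: analysis of only those present is an inference, and the silence on missing data is not itself a fault. What remains is that the method the article does state makes no use of T-1, so something would have to be added to it.

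Stronger readings are tempting, and the article does not support them:
- *That the follow-up effect will be biased, for example about 40% too small.* A shrinkage of that size (from 5 to about 3) needs loss running in opposite directions by arm. That is possible, but nothing in the article establishes it. Loss that depends on T-1 alike in both arms gives no bias when there is no effect.
- *That 20% will be lost after T-1.* The 20% is a general dropout allowance for the sample size, and the primary endpoint is at 3 weeks.
- *That the same number of points is at stake at 6 and 12 months.* Only the subjective part is collected then. The relative bias may carry over, but the points do not.
- *That a joint model removes the bias whatever the cause.* In these simulations loss depends only on observed values, so the joint model succeeds by construction.

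**Conclusion.** The concern holds in conditional form. The stated follow-up analysis leaves out information already collected on patients who are lost, and sits awkwardly with a main population of all randomised patients. If loss after T-1 depends on early response, the follow-up effect can be biased. For a true 5 points at both visits, the bias is about 0.1 to 0.9 points when the mechanism is the same in both arms, and about 1 to 3 points when it differs by arm. With the same mechanism and no effect at either visit, it is zero. These sizes rest on an SD of 17.5, 20% loss and the correlations shown, and are on the total-SFA scale at T-2. The T-1 primary comparison is unaffected.

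**What to change.** Keep the T-1 contrast as the primary comparison. Replace the repeated single-visit regressions with one mixed model for repeated measures per outcome: group, visit, group × visit, baseline and baseline × visit, with unstructured covariance, using all observed visits and taking the group contrast at each. Fit total SFA over T-1 and T-2 only. Fit the subjective SFA part and the VAS scales over T-1 to T-4. The subjective part is contained in the full SFA scored earlier, so nothing new is collected, provided that the subscore is kept in the record. Multiple imputation that includes T-1, followed by the stated regression, would serve equally.

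The cost is a change of analysis wording and a few lines of code, and no interim analysis is foreseen that it would disturb. The result would rely on missing at random given earlier visits. That is weaker than what the regression on completers needs, but it still fails if loss depends on later, unobserved recovery, such as a patient who stops answering calls after getting well. Patients with no value after baseline add nothing to the mixed model either, and the text should say so.

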### Secondary variables

After the first week of treatment, the level of confidence in the treatment is measured on a Treatment Credibility Scale (TCS) [23]. This was first proposed by Borkovec and Nau [24] and comprised four items that are assessed on a continuous VAS from 0 to 10 (0 totally disagree; 10 totally agree). The following elements are included, but at the baseline interview, only the first two questions are asked:

1. Are you confident this treatment will alleviate the pain you feel?

2. Does the treatment seem a logical one?

3. Would you recommend this treatment to a friend or relative who had the same problem?

4. Do you think this treatment could be applied to other problems?

After three weeks of treatment (T-1) (15 sessions of physiotherapy), the following secondary variables will be assessed by an independent evaluator:

• Pain intensity in the shoulder during the day, on a 10 cm VAS (DPI-VAS)

• Pain intensity in the shoulder during the night, on a 10 cm VAS (NPI-VAS)

• Degree of improvement perceived by the patient (IPP) (7 point Likert categoric scale: 0 much worse; 1 worse; 2 slightly worse; 3 no change; 4 slightly better; 5 better; 6 much better) [25]

• Degree of improvement perceived by the evaluator (IPE) (7 point Likert categoric scale: 0 much worse; 1 worse; 2 slightly worse; 3 no change; 4 slightly better; 5 better; 6 much better)

• NSAIDs taken (NT)

• Treatment Credibility Scale items 3 and 4

• Adverse events (ADEV) of a traumatic nature that might distort the results of the evaluation.

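### The ordered 7-point improvement scales are assigned to a chi-squared test on 6 degrees of freedom, which is valid but ignores the order and loses power against a consistent shift

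*Protocol article*

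**What the plan says.** The Secondary variables section of the protocol article lists "Degree of improvement perceived by the patient (IPP) (7 point Likert categoric scale") and "Degree of improvement perceived by the evaluator (IPE) (7 point Likert categoric scale"). Both use the same ordered anchors: "7 point Likert categoric scale: 0 much worse; 1 worse; 2 slightly worse; 3 no change; 4 slightly better; 5 better; 6 much better". IPP is collected at the end of treatment and at 3, 6 and 12 months. IPE is collected at the end of treatment and at 3 months. That makes six planned comparisons.

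The Data analysis section sets the rule for secondary outcomes: "the bivariate analysis will be performed using contingency tables analysed by ji-squared tests (for tables larger than 2 × 2"). Corrected chi-squared or Fisher's exact tests are named for 2 × 2 tables. The sentence ends "for the categoric variables, and by simple linear regression for all other cases". For the multivariate step it names two models: "When this is dichotomic, a binary logistic regression analysis will be made", and "For continuous variables, a multiple linear regression model will be used". The Treatment comparisons section adds "All the tests will be bilateral and carried out at a level of significance of α = 0.05".

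**The concern.** Read together, the label in one section and the rule in the other send IPP and IPE to a Pearson chi-squared test on a 2 × 7 table. The Pearson statistic does not change if the seven columns are put in any other order. To this test, a move from slightly better to better is no different from a move from slightly better to much worse.

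The hypothesis at the end of the Background section is directional: acupuncture plus physiotherapy should relieve pain and restore function more than the control does. On a global improvement scale, the natural form of that effect is a shift towards the upper end. A test that spreads its sensitivity over six degrees of freedom is inefficient against such a shift and could miss a real one. It also gives only a p-value, with no single measure of how large the shift is.

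**Working it through.** **Inputs from the protocol article.** Seven ordered levels and two arms; two-sided α = 0.05; 188 and 199 evaluable patients, 226 and 239 randomised, 20% dropout (Sample size and associated power). The article gives no power figure, expected distribution or effect size for IPP or IPE, so those are assumed below.

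**Check of the stated sample size.** It was set for the Constant score: means 70 and 65, SDs 17 and 18, power 0.80. With allocation in the ratio of the SDs, r = 18/17:

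n(experimental) = (1.960 + 0.842)² × (17² + 18²/r) / 5² = 7.849 × (289 + 306) / 25 = 186.8

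n(control) = 186.8 × 18/17 = 197.8

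Rounded up, these are 187 and 198 against 188 and 199 stated. The plan's figures reproduce to within one patient per arm.

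**Degrees of freedom.** (2 − 1) × (7 − 1) = 6.

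**Power without an assumed distribution.** If the group difference lies wholly along the order, the ordered 1-df test and the 6-df test share the same non-centrality λ. For 80% power on 1 df, λ = (1.960 + 0.842)² = 7.849. On 6 df the 5% critical value is 12.592, and the probability that a non-central chi-squared variable with λ = 7.849 exceeds it is 0.521.

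- 80% on 1 df becomes 52% on 6 df; 90% becomes 67%.
- For 80% power on 6 df, λ must be 13.62, and 13.62 / 7.849 = 1.74 times the sample.
- If only 4 to 6 of the 7 levels are used (3 to 5 df), 80% falls to between 64% and 56%.

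**Simulation under a proportional-odds shift.** Pearson chi-squared against the tie-corrected Wilcoxon test, 3,000 to 4,000 runs per setting. Four control distributions were assumed, in % from level 0 to level 6:

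- A: 1, 3, 6, 20, 30, 28, 12
- B: 2, 4, 8, 20, 28, 25, 13
- C: uniform
- D: 0.5, 1.5, 3, 15, 30, 30, 20

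The sizes 181 and 191 are 226 × 0.8 = 180.8 and 239 × 0.8 = 191.2.

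| Patients | Control distribution | Odds ratio | Chi-squared power | Wilcoxon power | Loss (points) |
|---|---|---|---|---|---|
| 181/191 | A | 1.5 | 31% | 59% | 28 |
| 181/191 | A | 1.6 | 42% | 73% | 30 |
| 181/191 | A | 1.7 | 54% | 82% | 28 |
| 188/199 | B, C, D | 1.5 | 31–34% | 59–61% | 26–28 |
| 188/199 | B, C, D | 1.68 | 53–55% | 80–83% | 27–29 |
| 226/239 | B, C, D | 1.5 | 40–41% | 68–70% | 28–30 |
| 226/239 | B, C, D | 1.68 | 61–64% | 87–89% | 24–26 |

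Losses are taken from the unrounded powers. With no effect, both tests reject in about 4% to 5% of trials.

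**The case against.** **The test is valid and the outcomes are secondary.** This stands. There is no bias and no excess of false positives. The primary analysis of the Constant score is a baseline-adjusted comparison and is untouched, and the day and night VAS pain scores fall under linear regression. The cost is efficiency on two scales.

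**The size is conditional.** This also stands. The distributions and odds ratios are assumed, and the simulated data follow the shift pattern that suits an ordered test. Against a non-monotone difference, for example more patients at both ends of the scale, the loss does not apply and the chi-squared test could be the more sensitive one.

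**The scores might be meant as the other cases sent to linear regression.** The protocol's own label says otherwise. If that was the intention, the text should say so: at 181/191 and odds ratios of 1.5, 1.6 and 1.7, a comparison of mean scores had 56%, 69% and 80% power, close to the rank test. The two readings therefore differ materially.

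**Stronger readings that the document does not support:**

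- A reader might infer that sparse cells at the worse end make the test unreliable. The article gives no distribution for these scales. Sparseness follows from an assumed one, and type I error stayed near 5% even then.
- A reader might infer that a significant result would show no direction. The planned contingency table and graphs would show it. What the test lacks is a summary effect estimate.
- A reader might infer that no adjusted analysis of an ordered response exists. The article is condensed and the analysis plan is not shown. Scoring or dichotomising the scale could properly be settled there.
- A reader might extend the point to the 0–3 medication scale. That scale is defined only for the baseline assessment, and the article does not say that it is reused for NSAIDs taken.

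**Conclusion.** The point holds as one of efficiency in a stated method, not of missing detail. The label and the rule together commit IPP and IPE to a test that discards the ordering and gives no summary effect. For a consistent shift, power falls from 80% to about 52%. Across the simulated settings with odds ratios of 1.5 to 1.7, the loss is about 24 to 30 points.

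This rests on the effect being a shift in one direction, which is how the trial's hypothesis would naturally appear on these scales, and on assumed distributions and effect sizes. The absolute powers depend on those assumptions. The gap between the tests varied little across the four distributions. A change is worthwhile, but it does not bear on the validity of the trial or on its primary conclusion.

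**What to change.** In the Data analysis section, take IPP and IPE out of the general rule for categoric variables. State that the arms will be compared with the Wilcoxon-Mann-Whitney test (or a linear trend test), and that a proportional-odds model will give the common odds ratio with 95% CI and serve for any adjusted analysis. Keep the frequency table by arm as description.

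This is a change of one or two sentences, with the same data and no additional patients. There are two small costs: the proportional-odds assumption has to be checked, and the ordered test is less sensitive to non-monotone differences, which the retained table would still let a reader see.

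### Baseline adjustment is fixed only for the SFA comparison: the pain analyses are not guaranteed the recorded baseline VAS, and the further-adjusted SFA model is built by outcome-driven forward selection and not ranked

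*Protocol article*

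**What the plan says.** All the analysis rules are in the Data analysis section of the protocol article.

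- **Primary outcome.** For the change in Constant SFA score, the groups "will be compared after adjusting by the baseline value and subsequently by other possible confounders". The confounders are not listed, and the section does not say which of the two results is the primary one.
- **Secondary outcomes, first step.** Categorical variables go to contingency-table tests; the rest are analysed "by simple linear regression for all other cases". Day and night VAS fall in this second class. A simple regression has one predictor, which for a treatment comparison is group.
- **Multivariate step.** This is described first for binary outcomes. The treatment group variable is forced, and a forward "method will be used to select the possible confounding variables in the model". Variables enter by a likelihood-ratio rule, for which no threshold is given.
- **Continuous outcomes.** Multiple linear regression is used, and "the same model-selection criteria and diagnostic procedures as described above will be applied". This covers both VAS scores and, on the natural reading, the later step of the SFA analysis.

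The baseline assessment (T-0) under Study variables records day and night pain on a 10 cm VAS. The abstract describes the pain outcomes as changes in VAS; the Secondary variables section lists only the VAS at three weeks.

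**The concern.** In a randomised trial the baseline value of a continuous outcome is usually the covariate most worth having, and it should be in the model by design. Here it is guaranteed for SFA and left open for pain. The authors see the point themselves: in the Background they fault an earlier acupuncture trial in shoulder pain for not adjusting its main outcome for baseline.

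The second issue is how the other covariates are chosen. Likelihood-ratio entry picks variables by their association with the outcome in the trial's own data. Randomisation already removes systematic confounding, so the reason for adjusting is precision, and that is best served by covariates named in advance. Selection makes the model unknown until the outcome data are seen, and the SFA comparison then yields two estimates with no stated order of authority.

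At stake are precision in the pain results and clarity about which SFA result is the trial's answer. The simple VAS regression remains unbiased under randomisation; it is only less efficient than it need be.

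**Working it through.** **The plan's own figure.** Inputs from Sample size and associated power: difference 70 − 65 = 5, SDs 17 and 18, two-sided α 0.05, power 0.80. With allocation proportional to the SDs, n_i = SD_i × (17 + 18) × (1.960 + 0.842)² / 5². This gives 186.8 and 197.8, so 187 and 198 against the stated 188 and 199. Power at 188/199 is 0.802. The calculation compares final means without adjustment, so nothing below changes the sample size. Two totals are used below: 387 (188 + 199) and 372 (465 × 0.8, those left after the stated 20% dropout).

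**VAS as change from baseline.** Take equal variance σ² at baseline and three weeks, and correlation ρ (assumed; the article gives none).
- Variance of the change: 2(1 − ρ)σ².
- Residual variance with baseline in the model: (1 − ρ²)σ².
- Ratio: 2(1 − ρ)/(1 − ρ²) = 2/(1 + ρ).
- Results: 1.82 at ρ = 0.1, 1.33 at 0.5, 1.05 at 0.9.

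**VAS as final score.** Assume an effect of 0.28 SD (close to the SFA planning effect, 5/17.5 = 0.29) and 186 per arm.
- Unadjusted: z = 0.28 × √(186/2) = 2.70; power = Φ(2.70 − 1.96) = 77%.
- Adjusted, ρ = 0.4: z = 2.70/√(1 − 0.16) = 2.95; power 84%.
- Adjusted, ρ = 0.5: z = 2.70/√(1 − 0.25) = 3.12; power 88%.

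**Would forward selection pick baseline VAS anyway?** For change scores the correlation of change with baseline is −√((1 − ρ)/2). With N = 387, the noncentrality of the likelihood-ratio statistic is −387 × ln(1 − r²). Entry is assumed at p < 0.05, a cut-off of 3.84.
- ρ = 0.5: r = −0.50, noncentrality 111, selection practically certain.
- ρ = 0.9: r = −0.22, noncentrality 19.8, selection probability 0.994.

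Over ρ from 0.1 to 0.9 the probability is at least 0.99. The loss therefore lies in the simple regression. In the multivariate model the fault is the missing guarantee.

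**Type I error for SFA.** These are simulations with no treatment effect, 3,000 trials each, so the Monte Carlo standard error near 5% is √(0.05 × 0.95/3000) = 0.4 points. The first used 12–15 candidate baseline covariates. The other two used 12 candidates, baseline-to-final correlation 0.5 and entry at 0.05. In the last, four candidates were prognostic, each worth 0.15 SD of the outcome per SD.

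| Scenario | Baseline-adjusted | Forward-selected | Either significant |
|---|---|---|---|
| N = 372 | 5.2% | 5.2% | 6.8% |
| N = 387, all candidates noise | 4.8% | 4.8% | 5.0% |
| N = 387, four weakly prognostic | 5.3% | 5.7% | 7.0% |

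In the last two rows the two models disagree on significance in 0.5% and 3.0% of trials.

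**The case against.** The strongest reply has four parts.

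- **Baseline SFA is already fixed.** This stands. A reader might infer from the forced-group rule that baseline SFA too is left to selection. The primary paragraph excludes that: baseline comes first, other covariates "subsequently" in its own order, so selection touches only the later SFA model.
- **Selection does no measurable harm to type I error.** This also stands. Forward selection alone gives 4.8% to 5.7%. The figure near 7% needs an analyst who may claim whichever SFA model is significant, and nothing in the article grants that.
- **Baseline VAS would be selected anyway.** Largely true in the multivariate model if VAS is analysed as change. It does not help the simple regression, which is the first stated analysis of pain.
- **An article leaves such detail to the full protocol or analysis plan.** This applies to the list of candidates and the entry threshold, whose absence is not the point here. It does not apply to the method. The article states simple regression for continuous secondary outcomes and outcome-driven selection for the adjusted models, and a plan that followed it would inherit both.

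A reader might also infer that a variable measured after randomisation, such as NSAIDs taken, could enter a model and bias the treatment effect. No sentence offers such a variable as a candidate. NSAIDs taken is listed as an outcome, and the baseline assessment supplies ample candidates, so that inference is not supported.

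**Conclusion.** The point holds as a correctable weakness in stated methods, not as an error that threatens the primary conclusion.

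Its main size is the precision lost in the VAS simple regression: a variance 1.33 times that of ANCOVA at ρ = 0.5 for change scores, or 7 to 11 percentage points of power for final scores at ρ = 0.4 to 0.5. These rest on an assumed effect and assumed correlations, and the trial is not powered on VAS.

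For SFA the issue is prespecification: the further-adjusted model is chosen from outcome data and its standing against the baseline-adjusted model is not stated. The documents do not support a claim that the plan inflates the type I error. About 7% is an upper illustration under an either-model claim with weakly prognostic covariates, and it falls to 5.0% if the candidates are noise.

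**What to change.** Three changes of wording in Data analysis:

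1. State that the primary result is the treatment effect on SFA change from the model with treatment and baseline SFA.
2. Analyse day and night VAS by linear regression with treatment and the baseline value of the same VAS, in place of the simple regression.
3. Remove forward selection from models that estimate treatment effects. Replace it with a short list of variables from the baseline assessment (T-0), named before the outcome data are examined, and label the resulting models as sensitivity analyses.

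The cost is wording only. Both baseline VAS scores are already collected and the sample size is unaffected. The article reports recruitment as still open and follow-up as planned to March 2007, so the change can precede the analysis.
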